### Ethical approval

The Intego procedures were approved by the KU Leuven Ethics Committee (nr. ML1723) and by the National Privacy Commission’s Sectoral Committee (decision nr. 13.026 of March 19, 2013). The procedures to collect data by Healthdata.be were approved by the Belgian Privacy Commission on April 17, 2018.

The protocol for this CRCT was approved by the Ethical Commission Research UZ/KU Leuven with number S62753 (May 13, 2019) and number S62753/0001 (March 20, 2020).

#### Trial registration

Registered on May 14, 2020, on ClinicalTrials.gov (number NCT04388228) https://clinicaltrials.gov/ct2/show/NCT04388228.

#### Informed consent

A researcher of the Intego network will be obtaining signed and written informed consent from each collaborating GP practice, and we will ensure that each GP practice is given a full explanation of the protocol in an information letter.

### Data collection

The data collection takes 12 months (see Fig. 1).

The data in the EHR of the Intego practices will be collected by HealthData through eHealth. This is part of the basic Intego project. This collection will be a snapshot of the EHR, which is used daily by GPs during consultation with patients. The data will be hosted on the Healthdata.be platform, which is described in more detail elsewhere [22].

Based on this data collection, the GPs will receive an A&F intervention with feedback reports on 4 different time points (every 3 months). At these time points, we will remind the GPs to work on their registration level of specific parameters or coded diagnoses in the EHR.

Every week, we will collect the data of the same practices, which is part of the basic Intego project. Then, for this A&F project, we will evaluate every 3 months whether the extended feedback led to a significant improvement in the registration level of the intervention group compared with the control group. We will analyze only the data of the practices that signed an informed consent form.

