### Allocation concealment and random sequence generation

The list of participating practices will be known at the start of the trial. The allocation sequence will be performed by a statistician (independent from the research group) and it will be generated using covariate-based constrained randomization [24]. More specifically, out of a list of all acceptable allocations one allocation scheme will be drawn at random. To balance the mean size of the practice between both groups, a list of all possible allocations (restricted to those allocations with equal number of practices in each group) with a maximal difference of 5% in mean number of patients per practice and a maximal difference of 5% in total number of patients will be created and one allocation will be drawn at random from this list [24]. The covariate-based constrained randomization procedure will be implemented using a SAS-macro [25]. If the trial would start before all practices are known, practices with “late entry” will be allocated using minimization [26], categorizing the number of patients per practice into 2 or 3 categories.

The control versus intervention group will be allocated in a 1:1 manner. GPs are not blinded to the intervention. The research facility will be blinded to the allocations until all data are collected.

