### Outcomes

Our primary outcome is the registration level of DM 2. This registration level will be expressed as the percentage of registered diagnoses of DM 2 in the EHR. The numerator will be the number of registered diagnoses of DM 2 in the EHR, and the denominator will be the number of patients with a prescription of diabetes medication (ATC classification A10) or with elevated levels of HbA1c (at least once > 53 mmol/mol) or with abnormal fasting glycemia (2 independent measurements > 126 mg/dl). For the primary outcome, we hypothesize that the intervention can achieve an improvement of 10% points (from 75% to 85%) in registration level within 12 months.

As a key secondary outcome, we will focus on the registration of CKD. The registration of CKD will be expressed as the percentage of registered CKD diagnoses in the EHR, with the numerator the number of registered diagnoses of CKD and the denominator the number of patients with a decreased (≤ 45 mL/min/1.73 m^2^) estimated glomerular filtration rate (eGFR). For the registration of CKD, we hypothesize the intervention can achieve an improvement of 20% points (from 50% to 70%) in registration level because preliminary analyses show the quality of registration of CKD is lower than for the primary outcome.

As exploratory secondary outcomes, we will evaluate the registration of heart failure, lifestyle factors (such as smoking and alcohol use), and biometric data (such as weight and length), and explore two EHR-extractable quality indicators for CKD and two for DM 2. The registration of heart failure will be expressed as the percentage of heart failure patients, with the numerator the number of registered heart failure diagnoses and the denominator the total active patient population older than 40. Lifestyle factors and biometric data will be expressed as the percentage of patients who have registered lifestyle factors or biometric data in their EHR.

The EHR-extractable quality indicators we will explore are as follows [27, 28]:
Percentage of patients with CKD, in whom the GFR, albuminuria, and total protein is determined at least once a yearPercentage of patients with CKD who are vaccinated with a pneumococcal vaccinePercentage of patients with DM 2 and an eGFR of < 30 mL/min/1.73 m^2^ who no longer receive metformin.Percentage of patients with DM 2 whose HbA1c level is measured at least once every 6 months

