### Power calculation

To measure an improvement in our primary and key secondary outcome, these are the percentage of registered DM 2 and CKD diagnoses in the EHR, a power calculation was performed.

To measure an improvement of 10% points (from 75% to 85%) in our primary outcome with 80% power, an alpha of 0.05, a variance inflation factor (VIF) of 21.12 (based on an intra-class correlation (ICC) of 0.103), we need 56 practices to be included in this CRCT, or 28 practices in each group (Table 2). To measure an improvement of 20% points (from 50% to 70%) in our key secondary outcome with 80% power, an alpha of 0.05, a VIF of 9.1, and an ICC of 0.32, we need 68 practices to be included in this CRCT, or 34 practices in each group (Table 2). To have enough statistical power to measure an improvement in both outcomes, 68 practices will be recruited. The VIF and ICC were calculated based on historical data from the Intego database and were used to correct for clustering.

**Table 2 Tab2:** Power calculation

	Assumed % correct diagnoses						Required number		
	C	I	Alpha	N0 (total)	ICC	VIF	Mean per practice	N patients	N practices

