**Key secondary**									
CKD	0.50	0.70	0.05	186	0.32	9.1	25	1693	68

Required total number of practices to have at least 80% power for the comparison of two proportions based on a logistic regression model correcting for the clustering of patients within GP practice. ICC and resulting VIF were obtained from historical data. The alpha level has been set at 5% for the primary endpoint and also at 0.05 for the key secondary endpoint (following a hierarchical closed testing procedure)

*C* control group, *I* intervention, *Alpha* alpha-level, *N0* total number of required diagnoses (patients) based on a *χ*^2^-test (hence, ignoring clustering within GP practices), *ICC* intra-class correlation, *VIF* variance inflation factor (taking into account differences in cluster size), *Cluster size* number of diagnoses per practice, *Mean per practice* mean denominator per practice, *N patients* total number of required diagnoses taking into account the clustering, *N practices* required total number of practices. The number of practices is rounded upwards such that an equal number of practices can be allocated to the control and the intervention group

A power calculation for our exploratory secondary outcomes was not performed.

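### Significance between arms is to be judged every 3 months, yet alpha is allotted once per endpoint and no confirmatory time point is fixed; the timing also sits uneasily with the stated blinding

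*Protocol article*

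**What the plan says.** All of the following is in the protocol article.

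- **Data collection.** "The data collection takes 12 months", with "feedback reports on 4 different time points (every 3 months"). For this project, "we will evaluate every 3 months whether the extended feedback led to a significant improvement in the registration level of the intervention group", with the control group as comparator.
- **Outcomes.** The primary hypothesis is worded as "we hypothesize that the intervention can achieve an improvement of 10% points (from 75% to 85%) in registration level within 12 months".
- **Power calculation and note to Table 2.** "The alpha level has been set at 5% for the primary endpoint and also at 0.05 for the key secondary endpoint". The note justifies using the same level twice by testing the two endpoints in order, "following a hierarchical closed testing procedure". Nothing is said about dividing alpha over time points.
- **Analysis.** A logistic GEE model is named, with the effect given as a difference in proportions and a 95% confidence interval. No time point is attached to it.
- **Allocation concealment and random sequence generation.** "The research facility will be blinded to the allocations until all data are collected".

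**The concern.** The Data collection sentence describes a comparison of arms judged for significance and repeated each quarter. It is worded as testing, not as description of a time course. The Outcomes section gives a horizon of 12 months, and a significant result at month 3 or month 6 also falls inside that horizon. As written, nothing prevents a claim from resting on whichever quarter reaches significance.

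Three things are at stake:

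- **Error rate of the primary claim.** It exceeds 5% if any quarter may count.
- **The hierarchy.** CKD may be tested only after DM 2 succeeds, but with four DM 2 results the text does not say which one opens the gate, or at which quarter CKD is then tested.
- **Blinding.** A quarterly comparison of arms, run while data are still being collected, is hard to square with a research facility that learns the allocation only at the end.

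**Working it through.** **1. What the sample size assumes.** Inputs from Table 2: 75% against 85% (DM 2) and 50% against 70% (CKD), alpha 0.05, power 80%, VIF 21.12 and 9.1, mean denominator per practice 192 and 25.

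Patients per arm, ignoring clustering, with p̄ the mean of p1 and p2:

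n = [1.960 × √(2p̄(1−p̄)) + 0.842 × √(p1(1−p1) + p2(1−p2))]² / (p1−p2)²

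- DM 2: (1.960 × 0.5657 + 0.842 × 0.5612)² / 0.01 ≈ 250 per arm, so N0 = 500 (stated: 500). 500 × 21.12 = 10,560; 10,560 / 192 = 55.0, which is 56 when made even (stated: 56).
- CKD: (1.960 × 0.6928 + 0.842 × 0.6782)² / 0.04 ≈ 93 per arm, so N0 = 186 (stated: 186). 186 × 9.1 = 1,692.6; 1,692.6 / 25 = 67.7, which is 68 (stated: 68).

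A one-sided test would give N0 = 394 for DM 2, so the stated figures correspond to one two-sided test at 0.05 per endpoint.

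**2. Number of looks.** 12 months / 3 months = 4, at months 3, 6, 9 and 12. This is inferred; the article does not state the number of tests.

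**3. Type I error if any quarter counts.** The quantity is P(at least one |Z| > 1.96) over four looks under the null hypothesis. The correlation between the quarterly test statistics is not given, so it is varied as an assumption (simulation, 1,000,000 draws per pattern).

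| Correlation | Same between all looks | Decaying with distance (value for adjacent looks) |
|---|---|---|
| 0.7 | 13.0% | 14.4% |
| 0.8 | 11.4% | 12.7% |
| 0.9 | 9.4% | 10.4% |
| 0.95 | 8.0% | 8.7% |
| 0.99 | 6.3% | 6.6% |

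For reference, the classical group-sequential pattern of independent increments gives 12.6%, and four independent tests give 1 − 0.95⁴ = 18.5%. Neither describes this trial well. The same practices are measured each time and registered diagnoses tend to persist, so high correlations, and hence the lower rows, are plausible.

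**4. Price of keeping four formal tests.** Bonferroni gives 0.05 / 4 = 0.0125 per look. With 68 practices the effective number per arm is 68 × 192 / (2 × 21.12) = 309 for DM 2 and 68 × 25 / (2 × 9.1) = 93 for CKD. The power of a single test then falls from 87.6% to 73% for DM 2 and from 80.2% to 62% for CKD. With one designated test at month 12 there is no loss.

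**5. Blinding, with the two statements side by side.** Collection lasts 12 months and the research facility stays blinded until it is complete. The evaluation of intervention against control is quarterly within that period. On the plain reading, the first three comparisons fall before the blind is lifted. The article does not mention deferral, coded arms or a separate analyst for them.

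**The case against.** The best defence is that month 12 is the natural analysis. The hypothesis has a 12-month horizon, the sample size is built on one test per endpoint, the Analysis section describes one effect estimate per outcome, and no stopping rule or early claim appears anywhere. On that reading the quarterly results only follow the course of the effect, and the type I error remains 5%. In addition, Fig. 1 (the time schedule) is not visible, and a full protocol or analysis plan may settle the status of the quarters.

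Much of this stands, and it rules out several stronger readings that a reader might infer:

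- **That the primary claim certainly has an inflated error rate.** The article never says that significance at any quarter suffices. The inflation is conditional on that rule.
- **That there is no alpha control at all.** The hierarchical procedure does control alpha across DM 2 and CKD. The gap concerns time points only.
- **That the blind will be broken.** The quarterly snapshots could be compared after collection ends, on coded arms, or by an independent party. The text does not say, so this is a tension and not a demonstrated breach.
- **That results by arm will bias the reminders to practices.** The audit is automated, and no section says that those who send reminders would see results by arm or act on them.

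What the defence does not remove is the sentence itself. The article commits to judging significance every quarter, alongside a single full alpha and blinding to the end. That is stated text in need of reconciliation, and not merely detail left to an analysis plan.

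**Conclusion.** The point holds in a conditional form. Quarterly significance comparisons are planned, alpha is allotted once per endpoint, and no visible section fixes the confirmatory time point. If any quarter may support the primary claim, the two-sided type I error is about 6% to 14%, assuming four looks and correlations between looks from 0.99 down to 0.7. If month 12 alone is confirmatory, it is 5%. In either case the gate from DM 2 to CKD has no defined quarter until the time point is named. The relation to the blinding statement is an ambiguity that the sections must resolve.

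**What to change.** In Outcomes, Data collection and Analysis, state the following: the confirmatory comparison for the primary and key secondary outcomes is at month 12 only, at two-sided 0.05, with CKD tested only if DM 2 is significant. Results at months 3, 6 and 9 are descriptive, given as estimates with confidence intervals and without a significance claim, and are produced by allocated arm only after all data are collected.

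This takes about two sentences, placed consistently in the three sections. Alpha stays at 0.05, the 56 and 68 practices stand, and outcomes and model are unchanged. The only cost is that no formal claim can rest on an earlier quarter.

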### Power calculation

To measure an improvement in our primary and key secondary outcome, these are the percentage of registered DM 2 and CKD diagnoses in the EHR, a power calculation was performed.

To measure an improvement of 10% points (from 75% to 85%) in our primary outcome with 80% power, an alpha of 0.05, a variance inflation factor (VIF) of 21.12 (based on an intra-class correlation (ICC) of 0.103), we need 56 practices to be included in this CRCT, or 28 practices in each group (Table 2). To measure an improvement of 20% points (from 50% to 70%) in our key secondary outcome with 80% power, an alpha of 0.05, a VIF of 9.1, and an ICC of 0.32, we need 68 practices to be included in this CRCT, or 34 practices in each group (Table 2). To have enough statistical power to measure an improvement in both outcomes, 68 practices will be recruited. The VIF and ICC were calculated based on historical data from the Intego database and were used to correct for clustering.

**Table 2 Tab2:** Power calculation

	Assumed % correct diagnoses						Required number		
	C	I	Alpha	N0 (total)	ICC	VIF	Mean per practice	N patients	N practices
**Primary**									
Diabetes	0.75	0.85	0.05	500	0.103	21.12	192	10,560	56
**Key secondary**									
CKD	0.50	0.70	0.05	186	0.32	9.1	25	1693	68

Required total number of practices to have at least 80% power for the comparison of two proportions based on a logistic regression model correcting for the clustering of patients within GP practice. ICC and resulting VIF were obtained from historical data. The alpha level has been set at 5% for the primary endpoint and also at 0.05 for the key secondary endpoint (following a hierarchical closed testing procedure)

*C* control group, *I* intervention, *Alpha* alpha-level, *N0* total number of required diagnoses (patients) based on a *χ*^2^-test (hence, ignoring clustering within GP practices), *ICC* intra-class correlation, *VIF* variance inflation factor (taking into account differences in cluster size), *Cluster size* number of diagnoses per practice, *Mean per practice* mean denominator per practice, *N patients* total number of required diagnoses taking into account the clustering, *N practices* required total number of practices. The number of practices is rounded upwards such that an equal number of practices can be allocated to the control and the intervention group

A power calculation for our exploratory secondary outcomes was not performed.

### Analysis

SAS software (SAS Institute Inc., Cary, NC, USA) and R (R Foundation for Statistical Computing, Vienna, Austria) will be used for analysis and for the graphs of the feedback. For this study, data will only be used on an aggregated level (per GP practice). Analysis will be performed using the numerator and denominator of each outcome per GP practice. The results will be reported according to the Consolidated Standards of Reporting Trials (CONSORT) [29]. The statistical model will not be adjusted by for any covariates.

To evaluate and explore the effect of the intervention on the primary and secondary outcome measures, a logistic generalized estimating equations (GEE) model will be used. This model is chosen because it can investigate the average response of an intervention on a population level. The effect of the intervention will be presented as the difference in proportions together with its 95% confidence interval. The GEE model will also be used to estimate the proportion of correctly registered diagnoses/parameters in the 2 allocated groups with their 95% confidence intervals.

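### The plan rules out all covariate adjustment, so it passes up a free gain in precision from each practice's baseline registration level, which is available and which the randomisation does not balance

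*Protocol article*

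**What the plan says.** Under Analysis, the protocol article says that "a logistic generalized estimating equations (GEE) model will be used", applied to each practice's numerator and denominator. It adds that "The effect of the intervention will be presented as the difference in proportions together with its 95% confidence interval". On covariates it is explicit: "The statistical model will not be adjusted by for any covariates". It gives no reason and no exception, so this is a stated choice rather than a detail left to a statistical analysis plan.

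Three places show that registration data exist from before the intervention:

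- Power calculation: "The VIF and ICC were calculated based on historical data from the Intego database and were used to correct for clustering".
- Outcomes: "preliminary analyses show the quality of registration of CKD is lower than for the primary outcome".
- Data collection: "Every week, we will collect the data of the same practices, which is part of the basic Intego project".

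The section on allocation describes covariate-based constrained randomisation with one purpose: "To balance the mean size of the practice between both groups". The constraints are a maximal 5% difference in mean number of patients per practice and in total number of patients. Registration level is not among them.

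**The concern.** The outcome is a practice-level percentage, and practices differ widely in it: the protocol's ICCs are 0.103 for DM 2 and 0.32 for CKD. If a practice that registers well at the start still tends to do so a year later, the baseline level explains part of the spread at month 12. A model that includes it compares the arms with less noise.

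Registration level is neither balanced by the design nor used in the model. The arms may therefore start apart by chance, and part of that gap stays in the single estimate the trial will report. CKD has the least reserve, because the 68 practices to be recruited are exactly the number its calculation requires.

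**Working it through.** **Inputs.** From Power calculation and Table 2:

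| | Control, intervention | N0 | ICC | VIF | Mean per practice (m) | Practices |
|---|---|---|---|---|---|---|
| DM 2 | 75%, 85% | 500 | 0.103 | 21.12 | 192 | 56 |
| CKD | 50%, 70% | 186 | 0.32 | 9.1 | 25 | 68 |

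The recruitment target is 68 practices, allocated 1:1, so 34 per arm. The correlation r is not in the document and is assumed.

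**Step 1: reproduce the plan's figures.** The two-proportion formula with pooled variance, two-sided alpha 0.05 and 80% power gives 250 per arm (500 in total) for DM 2 and 93 per arm (186) for CKD.

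- DM 2: 500 × 21.12 = 10,560; 10,560 / 192 = 55.0, rounded up to an even number: 56.
- CKD: 186 × 9.1 = 1,692.6; 1,692.6 / 25 = 67.7, rounded up: 68.

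Both match Table 2. At 68 practices the effective number per arm is 34 × m / VIF: 34 × 192 / 21.12 = 309.1 for DM 2 and 34 × 25 / 9.1 = 93.4 for CKD. Unadjusted power is 87.6% and 80.2%.

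**Step 2: size of a chance baseline gap.** The SD of a practice's observed level is √(p(1−p) × VIF / m), and the SE of the difference between arms is SD × √(2/34).

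- DM 2: SD = √(0.1875 × 21.12 / 192) = 0.144; SE = 0.0348, or 3.5 points; 95% range ±6.8 points.
- CKD: SD = √(0.25 × 9.1 / 25) = 0.302; SE = 0.0732, or 7.3 points; 95% range ±14.3 points.

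The chance of a gap of at least half the target effect, in either direction, is 15% for DM 2 (5 points) and 17% for CKD (10 points). About r times the gap passes into the unadjusted estimate. At r = 0.5, a 5-point DM 2 gap shifts it by about 2.5 points.

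**Step 3: what adjustment gains.** Adjusting for baseline multiplies the variance of the practice-level comparison by about 1 − r², so the interval width is multiplied by √(1 − r²). Power uses VIF × (1 − r²) at 68 practices.

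| Assumed r | CI width multiplied by | DM 2 power | CKD power |
|---|---|---|---|
| 0 (unadjusted) | 1.00 | 87.6% | 80.2% |
| 0.3 | 0.95 | 90.5% | 83.8% |
| 0.5 | 0.87 | 95.0% | 90.1% |
| 0.7 | 0.71 | 99.2% | 97.7% |

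**Step 4: is a useful r plausible?** The reliability of a practice's observed level is m × ICC / (1 + (m − 1) × ICC): 0.96 for DM 2 and 0.92 for CKD. Patient-level sampling noise would therefore weaken r little. Whether practices keep their rank over 12 months is a separate matter that the document does not settle.

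**The case against.** The strongest reply is that nothing in the planned inference is wrong. An unadjusted comparison of randomised arms is unbiased over allocations, its interval allows for chance imbalance, and Table 2 was built for this analysis. All of that stands. A reader might infer that the intervals are too wide or that the estimate is biased. The document supports neither reading: the intervals correctly reflect the design, and the 15% and 17% chances in step 2 come from the same variance that the VIF already covers.

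A reader might also infer that a baseline gap passes in full into the month-12 difference, or that the ICCs show stable differences between practices. Only about r times the gap passes through, and an ICC at one time says nothing about persistence. Persistence is plausible because coded diagnoses tend to stay in the record. Against it, both arms have the built-in audit and some feedback, which may move low-registering practices most, and the denominators change with prescriptions, laboratory values and recent consultations. At r = 0.2 the interval narrows by only 2%. The size of the gain is therefore uncertain.

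The case for adding practice size is weaker. It is already constrained to within 5%, leaving a constrained variable out of the model generally makes inference conservative, and nothing in the document shows that size predicts registration level.

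What the reply does not supply is any benefit from excluding the baseline level.

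**Conclusion.** The point holds as an efficiency improvement. The plan excludes a covariate that is available, that is not balanced by design and that is likely to be prognostic. The cost is lost precision and a residue of about r times any chance baseline gap, whose SE is 3.5 points for DM 2 and 7.3 points for CKD. The gain runs from small at r = 0.3 (interval about 5% narrower) to large at r = 0.7 (about 29%). CKD stands to gain most, since it has 80.2% power and nothing to spare.

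These figures rest on the protocol's own ICC, VIF and denominators, on 34 practices per arm, on an assumed r, and on the usual 1 − r² approximation carrying over to the logistic GEE with a standardised difference. That every practice's baseline level can be obtained is read from the routine extraction and the historical data described. The document does not support calling the planned analysis biased, invalid or underpowered.

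**What to change.** Replace the sentence under Analysis with wording such as: *The primary GEE model will include the practice's registration level of the same outcome at randomisation. The difference in proportions and its 95% confidence interval will be obtained by marginal standardisation. The unadjusted result will be reported as a sensitivity analysis.* Practice size may be added because it constrained the randomisation, but this is optional.

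Enter the baseline level as a proportion, or as an empirical logit with a continuity correction. A plain logit is undefined at 0% or 100%. With the CKD inputs (50%, ICC 0.32, 25 per practice) and an assumed beta-binomial with equal denominators, about 7% of practices, roughly 5 of 68, would sit at one of those values and drop out. The logit form also needs a numerator confined to the patients in the denominator, which the Outcomes section does not state; the plain proportion avoids this.

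The cost is the revised wording, the choice of covariate scale and one baseline extraction from data already collected. No extra practices are needed. Standardisation keeps the planned effect measure and its population-average meaning, and a practice-level covariate fits the aggregated data. The change should be fixed before the allocations are unblinded, so that it cannot look data-driven.
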